### Study setting

Our study is set in the isolated, mountain district of Jumla, Nepal. Nepal is a poor country with a Human Development Index 0.54, a rank of 145 out of 187 countries [26]. Jumla has an Human Development Index of 0.35, with a rank of 68 out of 75 districts in Nepal, making it one of the poorest and most disadvantaged districts in an already impoverished nation [27]. There has been little health research done in Jumla, although it was the first region to introduce community based management of childhood pneumonia [28–31]. Most of the population (88.7 %) live in small mountainside villages and eke a bare living from subsistence agriculture [32]. International Nepal Fellowship has agreed to host our research. They have been working in Jumla since 1978, initially offering outpatient and inpatient leprosy and tuberculosis care, later expanding their services to include a Community Development and Rehabilitation team. International Nepal Fellowship has a policy of social inclusion and poverty alleviation. They purposefully include women, low caste people and people living with disabilities in all of their programmes. International Nepal Fellowship has 56 women’s self-help groups, each comprising approximately 20 to 25 women, in two village development committee areas. The groups were formed following extensive community and local government consultation to find villages with the most poor and marginalised people. Consent and participation by villagers eventually led to the formation of the self-help groups. The groups have a distinct geographical catchment within the village and contain neighbours and extended family members. Each group has a monthly meeting facilitated by community workers. At the group meetings members discuss and participate in microfinance, income generation, health education and community mobilisation. Our research is set within these women’s self-help groups.

### Study population

The participants are members of the existing women’s self-help groups and their household children age 12 and under. All members of the study groups will be invited by International Nepal Fellowship staff to participate. In this setting it is likely that all members will agree to participate as the burden on them is very slight. Women who live in a household with a child aged 12 and under will be included in the survey since rural Nepalis mostly live in extended family groups and mothers-in-law are important decision-makers for child health [33–35]. CSOM is a chronic condition and occurs at all ages, with a peak in early childhood. The age of 12 has been chosen as the upper limit as most young children continue to live with their families and attend local schools. Older children are increasingly moving to the district capital for the later years of high school, which would make followup assessment difficult.

### Inclusion criteria

Women, aged 18 years and over, who are attending International Nepal Fellowship women’s self-help groups in Jumla and who have a child aged 12 years and under living in their householdThe children aged 12 years and under who live in the household of participant women

### Exclusion criteria

Women under the age of 18 yearsWomen who do not have a child aged 12 years and under living in their householdWomen who cannot give informed consent because of infirmity or illnessChildren over the age of 12 yearsParticipants will not be paid or rewarded individually for their participation (Fig. 1).

**Fig. 1 Fig1:**
[figure not shown]
Study design

### Content of the intervention

The intervention is community-based and participatory and it will not be possible for participants to be blinded after allocation. The design of the intervention is greatly dependent upon the interviews from our exploratory qualitative study. Those interviews with women revealed that they enjoy meeting and learning together in their groups and that they had a strong preference for visual and interactive presentations. Three sessions will take place within the existing regular monthly meeting of the women’s self-help group meeting in the intervention groups. The intervention is based on the WHO *Primary Ear Care Training Programme*, which has been widely adopted in India and other low resource settings. The basic level of the programme aims to educate parents, carers and community health workers about ear infections, their recognition, risk factors, prevention, risk of hearing loss and appropriate care-seeking [21]. Session 1 and Session 2 will be facilitated by the field team leader. Session 3 will be completed by the usual group facilitator. Recap of previous sessions is a normal part of their group meetings. The content of each session is standardised. Attendance at each session will be recorded and a sensitivity analysis performed.

#### Session 1

The first session is an interactive education session using drama and pictures. We have developed a new resource using local photographs based on the *WHO Primary Ear Care Training Programme—Basic Level.* The first of four components shows the importance of the ear and the sense of hearing—demonstrating the usefulness of being able to hear every day noises such as a baby crying, conversation, dogs barking and, for children, hearing in the busy classroom. The second component is identifying signs and symptoms of ear infections including ear pain, discharge, pulling at ears, fever and irritability. The third section details the transmission of ear infections via coughing, sneezing, touching and dirty water. The final section examines ear care, not putting anything in the ear, such as sticks, oil or any or substance, encouraging appropriate care seeking at the local health post and explaining about the medications that will be provided there.

#### Session 2

The second session is a practical session learning hands-on mopping of the ear and correct installation of drops, along with reinforcement of the messages from the first session. This is a very important session as there is little instruction given in the Nepali health system. The diagnosis and treatment is often very appropriate and health posts deliver care at no cost to the patient, but there is frequently a lack of patient engagement, explanation, question answering and demonstration. Therefore, since ear wicking and installation of drops must be performed repeatedly at home to work effectively, it is necessary for care-givers to master the technique.

#### Session 3

The third session is a brief recap of sessions one and two and will include a small laminated card for each woman to take home with pictures of ear-wicking and drop installation in a child’s discharging ear. Each session will be responsive to the cultural context of village life and the extremely difficult daily lives of the women. Participation will be sought at every step and sessions adapted to women’s expressed understanding, questions and needs.

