**Methods/design:**

Using 56 existing women’s self-help groups, sample size, adjusting for clustering and data analysis, is set at 15 groups per arm. A baseline survey of 30 randomly selected groups will be performed, consisting of a knowledge, attitude and practice questionnaire aimed at women who participate in self-help groups, as well as examination of their children’s ears. This will be followed by random allocation, stratified by geography, into 15 intervention and 15 control groups. The intervention groups will participate in three interactive educational sessions at their regular monthly meetings based on *World Health Organisation Primary Ear and Hearing Resource, Basic Level.* The control groups will continue their usual monthly group meetings. At 12 months, a follow-up assessment of both control and intervention groups will be performed, with a repeat women’s survey and repeat ear examination of the children. Data analysis will be by intention to treat and clustering will be considered at every stage. Cluster level data will be analysed using *t*-test and individual level data using mixed effects linear regression and logistic regression random effects model as appropriate.

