### Outcome measures

#### Primary outcome measure—the questionnaire

The survey instrument for women in the intervention and control groups is a questionnaire. The primary outcome measure is a 25 % difference in knowledge, attitude and practices, regarding ear disease in their children, of women in the intervention group compared to the control group. There are demographic questions such as age, number of children, maternal education, food security, usual health practices followed by questions about knowledge, attitude and practice regarding ear health, hearing, ear disease and health care seeking. The questionnaire uses already validated questions from the Demographic Health Survey (DHS) and Multiple Indicator Cluster Survey (MICS) performed recently in Nepal and is informed by a similar survey conducted in South India [32, 36, 37]. Other questions have been inspired by the *Primary Ear and Hearing Care Training Resource* and the literature on health care engagement [21]. The knowledge section asks the question ‘what do women know about ear infections in their children’, what are the local causes, treatments and complications. The attitude section queries ‘what do women think about ear infections’, is there a low level of ‘threat perception’, are there cultural barriers to seeking care, is there a perception of poor quality care or that ear infections are incurable. Finally, the practice section inquires what they do about them, whom they consult, if anyone, what would help them seek care and whether they know what care is available. The questionnaire has been pre-tested in Australia with a small adjustment made to a single question. The duration in English with educated mothers is 10 mins. Pretesting with village women on the terai (plains) did not reveal any difficulties with the questionnaire. We then undertook a formal pilot study of 20 village women in Jumla, attending INF clinics in Jumla Bazaar, to check for length, understanding and clarity. For these uneducated and illiterate women, the survey was too long and several questions incomprehensible to them. The questionnaire was edited appropriately and five questions removed from the demographic section. The new questionnaire was clear and can be completed in 10-15 mins. The questionnaires will be completed on paper in Nepali by the research assistants trained by the field team leader. Training will take place over two days in Jumla bazaar. A number of interviews will be observed by the field team leader to ensure quality control and all forms will be reviewed regularly to ensure correct completion by assistants. Baseline assessment will be performed prior to allocation into intervention and control groups to avoid bias. Group attendance and financial records are strictly kept at each meeting so it is not possible for an outsider to attend a group meeting unobserved. It is possible that there could be contamination of the control group by an intervention group member offering advice. This is not very likely as extended family mostly live side by side, meaning that grandmothers, aunties and mothers, who might share childcare and advice, are in the same group, or cluster. There are few sources of health information for these mainly illiterate women in this remote region. Followup assessment will be performed 12 months after baseline assessment. The trained research assistants performing followup assessment will be blinded to allocation.

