### Sample size calculation

The sample size is calculated on the primary outcome. Using data extracted from questions in the previous qualitative study, sample size for an unclustered study with a 5 % two sided Type 1 error and 80 % power to detect a 25 % difference in mean questionnaire score, would be 114 women in each arm. Both Daly et al. in USA and Srikanth et al. in India found a very low level of knowledge about causes and risk factors for otitis media in mothers of young children [37, 40]. We anticipate a similarly low level in Jumla, and hypothesise that a 25 % increase would be modest and achievable. The cluster sizes are set at the size of the women’s groups which is around 20 women. To adjust for clustering, it is necessary either to establish an approximate intra-cluster correlation coefficient (ICC) or ρ, which measures the similarity of individual responses within clusters, in order to calculate the design effect (the number by which an individual trial must be multiplied to adjust for clustering) or to calculate the between cluster variability, k. These values vary and any estimate can only be approximate. Other studies on neonatal mortality in women’s groups in Nepal have found a very low ICC of 0.00644 [24]. Tielsch et al. [41] calculated a design effect of 1.23 with their study of supplements to prevent malnutrition in children. Mullany et al. [22] used a design effect of 2.0 for their study looking for a 25 % reduction in omphalitis in newborns in rural Nepal. Slightly further afield in Bangladesh, Aboud et al. [23] calculated an ICC of 0.03 for a responsive feeding and stimulation intervention to clusters of rural women and children. Pagel et al. [42] reviewed ICC for interventions around perinatal outcomes in low resource countries and found universally low ICC for maternal and neonatal mortality but higher ICC for other interventions such as skilled birth attendance. For example, in India and Bangladesh skilled birth attendance ranged from ICC 0.02-0.04. The Design Effect (DEff) is the number by which the sample size for an individual randomised controlled trial must be multiplied to give the equivalent power to a cluster randomised trial. The Design Effect also considers the number of individuals in each cluster *– m.* Using the equation DEff = 1 + (*m*-1) ρ, assuming ρ = 0.03, would give a DEff = 1.6, or 182 women per arm. Using the safe equation DEff = 1 + (m-1) ρ, assuming ρ = 0.05, would give a DEff = 1.95, or 223 women per arm. This would translate into 11 clusters per arm. To account for stratifying, we have added a conservative extra two clusters per arm, which would make 13 clusters per arm. To enable robust cluster analysis a minimum of 15 clusters is ideal. This will provide a generous total sample of approximately 600 women in 30 clusters, 15 in the intervention and 15 in the control arm.

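### The contamination argument leaves out the host organisation's group facilitators, who deliver Session 3 while the same organisation's workers run the control meetings

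*Protocol article*

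**What the plan says.** - **Who runs the meetings.** Study setting places all 56 groups under one organisation, in two Village Development Committees. "Each group has a monthly meeting facilitated by community workers", and health education is among the listed activities.
- **Who delivers the intervention.** Under Content of the intervention, the field team leader gives Sessions 1 and 2 within the regular meeting. For the last session: "Session 3 will be completed by the usual group facilitator. Recap of previous sessions is a normal part of their group meetings". Session 3 is a short recap of the first two and includes a take-home picture card.
- **Control condition.** The abstract's Methods/design says: "The control groups will continue their usual monthly group meetings".
- **Contamination.** Study design judges co-interventions unlikely because no other non-government organisation works directly with these women. The section on the primary outcome says that an outsider could not attend a meeting unnoticed. It then adds: "It is possible that there could be contamination of the control group by an intervention group member offering advice", and judges this not very likely.
- **Timing.** The sessions fill three consecutive monthly meetings after baseline, and follow-up is 12 months after baseline.

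**The concern.** The article does not leave contamination to another document. It argues the point and concludes that the risk is low, but none of its three arguments reaches the facilitators. The absence of other agencies says nothing about spread through the host's own staff. A facilitator is not an outsider at a meeting, and is not a group member giving advice to a neighbour.

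A worker who gives the recap must know the content. If that worker also runs a control group, the recap could be repeated there as ordinary health education. With three monthly sessions and follow-up at 12 months, up to about nine months of control meetings remain (12 − 3 = 9). The article itself notes that these women have few sources of health information, which makes the monthly meeting a more important channel.

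The primary contrast is at stake. Spillover would raise control scores and bias the difference in mean questionnaire score towards zero. A small or null result would then be hard to tell from a diluted comparison. The planned sensitivity analysis on attendance concerns the intervention sessions, so it would not show exposure in control groups.

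**Working it through.** **Routes compared with the article's arguments**

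| Possible route into control groups | Addressed in the article? |
|---|---|
| Another organisation's programme | Yes, Study design |
| Outsider attending a meeting | Yes, primary outcome section |
| Advice from an intervention group member | Yes, primary outcome section |
| Host's facilitator carrying Session 3 content | No |

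**Inputs** (Sample size calculation): "5 % two sided Type 1 error and 80 % power"; "detect a 25 % difference in mean questionnaire score, would be 114 women in each arm"; "The cluster sizes are set at the size of the women’s groups which is around 20 women"; ICC 0.03 or 0.05; 15 groups per arm. No mean or SD is printed.

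**The plan's own figure.** Design effect = 1 + (m − 1)ρ.
- ρ = 0.05: 1 + 19 × 0.05 = 1.95, and 114 × 1.95 = 222.3, rounded up to 223. This matches the article.
- ρ = 0.03: 1 + 19 × 0.03 = 1.57, and 114 × 1.57 = 179. With the rounded design effect of 1.6 it is 182.4, against 182 stated.

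The article attributes the increase from 11 to 15 groups per arm to stratifying and to robust cluster analysis. None of it is an allowance for contamination.

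**Planning effect, back-solved from 114 per arm.** d = √(2/114) × (1.960 + 0.842) = 0.371 SD.

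**Dilution.** Let c be the share of the contrast that is lost, so the effect becomes 0.371 × (1 − c). The article gives no value for c, so every c below is an assumption. The standard error of the difference with 15 × 20 = 300 women per arm at ICC 0.05 is √(2 × 1.95/300) = 0.114. Power is from a non-central t with 28 degrees of freedom and noncentrality 0.371(1 − c)/0.114.

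| c (assumed) | Effect, SD | Noncentrality, ICC 0.05 | Power, ICC 0.05 | Power, ICC 0.03 |
|---|---|---|---|---|
| 0 | 0.371 | 3.25 | 88% | 94% |
| 10% | 0.334 | 2.93 | 81% | 88% |
| 20% | 0.297 | 2.60 | 71% | 80% |
| 30% | 0.260 | 2.28 | 60% | 69% |

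**How much dilution the design can absorb.** By the normal approximation, power stays at 80% or more up to c = 1 − √(114/n), where n is the effective number per arm.
- ICC 0.05: n = 300/1.95 = 153.8, so c = 14%.
- ICC 0.03: n = 300/1.57 = 191.1, so c = 23%.

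The cluster t-test is slightly less forgiving: at ICC 0.05, power is already down to 81% at c = 10%.

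**Reading c.** c is the share of control groups exposed multiplied by the share of the effect passed on. If 3 of 15 control groups received the full effect, c = 20%. If they received half of it, c = 10%. The calculation spreads the loss evenly over the control arm and ignores any extra between-group variance from uneven exposure.

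**The case against.** The strongest reply is that the key link is inferred. A reader might conclude that the same facilitators sit through the training and then run control meetings. The article does not say so. It gives neither the number of community workers nor their assignment to groups. It does not say that they attend Sessions 1 and 2, and it describes no training of facilitators in the ear material. A reader might also infer from the geographic stratification that neighbouring groups are split between arms and share a worker. Stratifying by Village Development Committee, remoteness and distance to the road shows neither.

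Further, the facilitator gives only a brief recap, while the drama and the hands-on practice come from the field team leader. An informal repeat is unlikely to carry the full effect. The design also has some spare power, and bias towards zero cannot create a false positive. Finally, staff rosters and instructions are operational detail that a condensed article may leave to the full protocol.

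Most of this stands, and it limits the point to a gap in the argument plus a conditional risk. Two things remain. The article makes its own case that contamination is unlikely, and that case omits a channel which its choice of deliverer for Session 3 opens. Spare power also protects only the test: it does not remove bias from the estimated difference.

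**Conclusion.** The point holds in a limited form. The article assigns Session 3 to the usual facilitator, keeps control meetings running under the same organisation's workers, and offers a contamination argument that does not cover them. Whether any facilitator serves both arms is not stated. If none does, most of the concern closes.

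If some do, the primary difference would be biased towards zero by an amount that the article does not allow anyone to calculate. The fall in power from about 88% to 81% at 10% dilution and 71% at 20% is an illustration. It rests on an assumed dilution, an effect back-solved from 114 per arm, ICC 0.05 and groups of 20. It should not be read as a demonstrated loss.

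**What to change.** 1. Before Session 1, list the facilitator of each of the 30 groups and mark anyone who serves both arms. The article reports that data collection has begun, so if sessions have already started, compile the list now.
2. Instruct all facilitators not to use the trial's ear material or cards in control groups until the 12-month follow-up is complete. This concerns teaching material only and leaves the article's referral arrangements as they are.
3. Add a line on any ear-health content to the control-group meeting record. The article mentions only attendance and financial records, so this is a new entry.
4. Where a facilitator serves both arms, the field team leader may give the Session 3 recap. The cost is less uniform delivery across intervention groups and a less complete hand-over to local staff. It would not undo what a facilitator has already heard if present at Sessions 1 and 2.
5. Leave out individual questions on exposure (session heard, card seen), or ask them only after every scored interview in that group is finished. Allocation is by group, so one positive answer could reveal the arm to a blinded assistant who still has other members to interview.
6. Extend the contamination statement in the primary outcome section to cover facilitators.

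The core cost is one list, one instruction, one extra line in a record and a sentence or two of text.

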### Outcome measures

#### Primary outcome measure—the questionnaire

The survey instrument for women in the intervention and control groups is a questionnaire. The primary outcome measure is a 25 % difference in knowledge, attitude and practices, regarding ear disease in their children, of women in the intervention group compared to the control group. There are demographic questions such as age, number of children, maternal education, food security, usual health practices followed by questions about knowledge, attitude and practice regarding ear health, hearing, ear disease and health care seeking. The questionnaire uses already validated questions from the Demographic Health Survey (DHS) and Multiple Indicator Cluster Survey (MICS) performed recently in Nepal and is informed by a similar survey conducted in South India [32, 36, 37]. Other questions have been inspired by the *Primary Ear and Hearing Care Training Resource* and the literature on health care engagement [21]. The knowledge section asks the question ‘what do women know about ear infections in their children’, what are the local causes, treatments and complications. The attitude section queries ‘what do women think about ear infections’, is there a low level of ‘threat perception’, are there cultural barriers to seeking care, is there a perception of poor quality care or that ear infections are incurable. Finally, the practice section inquires what they do about them, whom they consult, if anyone, what would help them seek care and whether they know what care is available. The questionnaire has been pre-tested in Australia with a small adjustment made to a single question. The duration in English with educated mothers is 10 mins. Pretesting with village women on the terai (plains) did not reveal any difficulties with the questionnaire. We then undertook a formal pilot study of 20 village women in Jumla, attending INF clinics in Jumla Bazaar, to check for length, understanding and clarity. For these uneducated and illiterate women, the survey was too long and several questions incomprehensible to them. The questionnaire was edited appropriately and five questions removed from the demographic section. The new questionnaire was clear and can be completed in 10-15 mins. The questionnaires will be completed on paper in Nepali by the research assistants trained by the field team leader. Training will take place over two days in Jumla bazaar. A number of interviews will be observed by the field team leader to ensure quality control and all forms will be reviewed regularly to ensure correct completion by assistants. Baseline assessment will be performed prior to allocation into intervention and control groups to avoid bias. Group attendance and financial records are strictly kept at each meeting so it is not possible for an outsider to attend a group meeting unobserved. It is possible that there could be contamination of the control group by an intervention group member offering advice. This is not very likely as extended family mostly live side by side, meaning that grandmothers, aunties and mothers, who might share childcare and advice, are in the same group, or cluster. There are few sources of health information for these mainly illiterate women in this remote region. Followup assessment will be performed 12 months after baseline assessment. The trained research assistants performing followup assessment will be blinded to allocation.
